**Methods/design:**

This study aims to provide a better understanding of the relationship between cognitive complaints, depression, and objectively measured cognitive impairment in HIV, and of the key factors, whether biological or personal, which relate to these presentations and to their evolution over time. Characterization of this heterogeneity will permit more focused pathophysiological studies, and allow more targeted interventions. The project makes extensive use of Web-based research and health care delivery tools, aiming to provide cost-effective, “clinic ready” tools to improve brain health in HIV. This project has two overarching aims, reflecting our dual goals of understanding and improving brain health in HIV, focusing on cognitive impairment, its contributors and consequences.

The objectives are to contribute evidence for the validity of a brief brain health assessment, to estimate the extent to which HIV-related cognition-relevant clinical factors and patient-centered outcomes inter-relate and evolve over time, allowing identification of the mechanisms underpinning longitudinal change in brain health and to contribute evidence for the feasibility, effectiveness potential, acceptability, and underlying mechanisms of promising interventions for optimizing brain health. We adopt a cohort multiple randomized control trials design. A total of 900 participants will be characterized prospectively over a 27-month period to answer questions about the evolution of outcomes of interest. All participants will be offered basic brain health self-management information. Sub-groups will participate in pilot studies of specific, more intensive interventions to provide pragmatic evidence for feasibility, effectiveness, and comparative effectiveness.

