The nomenclature describing cognitive impairment, and the modalities used to measure cognition vary across clinical disciplines, hindering interdisciplinary research. Here, we have chosen to use the term cognitive deficit and its positive opposite, cognitive ability; we also distinguish between directly measured cognitive deficits (i.e. neuropsychological tests) and perceived cognitive deficits reported as symptoms (here measured using validated questionnaires). This method is broadly consistent with the requirements of the current diagnostic criteria for HAND [3]. Our view of cognition departs from current categorical diagnosis, focusing instead on cognitive ability as a “quantity” [19]. We propose that declines in cognitive ability compared to the individual’s own baseline will be the most useful trigger for intervention, and that stability or improvements are likely to be more important to the patient than whether they meet strict diagnostic thresholds. Rigid use of diagnostic categories may prevent recognition of real difficulties, and limit access to useful interventions for patients with high (but deteriorating) cognitive abilities [20, 21].

Current approaches to diagnosis of HAND rely on neuropsychological testing [3]. This is resource-intensive, with restricted availability. Front-line health care providers who must judge whom and when to refer are poorly equipped to respond to patients’ concerns about cognition: What symptoms signal difficulties that warrant further investigation or intervention? What interventions are appropriate? Are there patients who do not report symptoms who nonetheless have deficits and would benefit from assessment and treatment? We recognize that a key challenge in this area is to understand the link between what patients are saying, which is what matters to them, and what the objective tests indicate. Further, we need to better understand the relationship between different facets of brain health, address these within an interdisciplinary framework, and characterize their evolution over time. Developing better ways to measure both symptoms and signs that are feasible in everyday practice and tuned to the full range of abilities in this population is a crucial first step.

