### Study population

The target population is people in middle age and older, the group felt to be most at risk of both longer-term effects of HIV infection and the interaction between these and aging-related brain changes: Inclusion criteria are age ≥35, HIV+ for at least 1 year, able to communicate adequately in either French or English, and able to give written informed consent. If necessary, we will oversample patients >60 years old and women to ensure at least 100 of each are enrolled. The focus is on milder cognitive deficits, which is the area of greatest clinical uncertainty. Thus, exclusion criteria include dementia (MoCA <18) [25], or treating physician’s concern about capacity to consent, life expectancy of <3 years or other personal factor limiting the ability to participate in follow-up, non-HIV-related neurological disorder likely to affect cognition, known active CNS opportunistic infection or hepatitis C requiring Interferon-based treatment during the follow-up period, psychotic disorder, or current substance use disorder or severe substance use disorder within the past 12 months. Individuals with current or past major depressive disorder are eligible for the core project, and indeed will be the focus of one of the studies under our third aim. There are additional inclusion/exclusion criteria for individual sub-studies, described below. A brief questionnaire is used to identify characteristics of all persons approached for recruitment to determine whether non-participation introduces a selection bias into our study.

The core of the research program is the development and follow-up of a comprehensively characterized cohort of persons with HIV. The cohort is being assembled through consecutive sampling from five clinics in several large cities in Canada: Montreal, Toronto, Hamilton, and Vancouver. These clinics collectively manage thousands of patients, with diverse demographic and HIV risk profiles, most of whom are routinely followed at 3 month intervals. A total of 900 participants will be comprehensively assessed and followed longitudinally at 9 month intervals over a 3 year period (four assessments).

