Sample size for SEM is large: optimally 15 to 20 people per parameter estimated. The number of parameters estimated in a complex model can be substantial (approximately three per included latent variable) therefore sample sizes in the range of 400 to 600 are needed for the Wilson-Cleary model. Given the focus on cognition, it will be informative to identify if the structure and relationships between and among variables differ in the presence of lower cognitive ability. As we are expecting about 40 % to have some cognitive deficit, a sample size of 900 would yield about 360 persons for an SEM model. The model will also be fit longitudinally, providing the opportunity to understand how changes in key constructs affect brain health and function over time.

To address heterogeneity of the HIV population in terms of evolution of cognitive ability over time, and co-evolution of cognitive ability with antecedent variables, correlates and consequences, a form of latent trajectory analysis (group-based trajectory analysis; GBTA) [37] will be used. This analysis is optimized with four or more time points. This approach has been used to characterize evolution of cognitive impairment over time in an elderly population [38, 39], and apathy in a stroke population [38]^5^. GBTA assumes the population is made up a mix of people with different longitudinal trajectories and uses a semi-parametric approach to group like with like. The optimal number and shape of trajectories is determined by theory, Bayesian Information Criteria (BIC), magnitude of the average posterior probability of group assignment (with ≥0.70 recommended), and closeness of the theoretical and assigned proportions of people to trajectories [37].

The sample sizes projected for this study should yield up to 5 to 7 distinct trajectories [40], providing a detailed view of the heterogeneity of longitudinal change and of factors contributing to trajectory of change. Additional multivariate approaches may be warranted, such as mixed models, to assess the impact of key variables on longitudinal change in brain health.

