#### Aim 2. To contribute evidence for the validity of a brief brain health assessment approach (B-CAM)

The strength of the relationship between the results of the reference standard cognitive assessment and the B-CAM will be tested using rank correlation and sensitivity and specificity. To formally estimate the sensitivity and specificity of B-CAM, we will use the classical method of Begg and Greens [41], which assesses diagnostic tests when there are different verification probabilities. Because the new measure, B-CAM, is mapped to a standard normal distribution (on a logit scale), it is possible to use the distribution to identify a cut-point for further testing. Validation will take place on the first 500 consecutive persons enrolled. The sample size for this estimation is based on the formula provided by Begg and Greens for sensitivity, specificity and corresponding 95 % confidence intervals (CI). Assuming that approximately 40 % of people will score in a range indicative of cognitive deficit on B-CAM, we will recruit 100 % of all those with B-CAM evidence of deficit (500 * 0.4 = 200) plus 20 % of the remainder (300 * 0.2 = 60). With this verification strategy, and under the assumptions above, the estimated sensitivity is 0.86 (95 % CI: 0.73 to 0.93). The corresponding values for specificity are 0.93 (95 % CI: 0.89 to 0.96). We will also estimate the effect of covariate status (age, co-infection with hepatitis C, history of drug use, recent immigrant, or low education) on sensitivity and specificity.

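### The numerical criteria for choosing the number of trajectories cannot tell stable differences in level from differences in change, so the number of groups is not evidence of heterogeneous change

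*Protocol article*

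**What the plan says.** The Aim 1 part of the statistical methods adopts GBTA to address heterogeneity in how cognitive ability evolves. Its selection rule is: "The optimal number and shape of trajectories is determined by theory, Bayesian Information Criteria (BIC), magnitude of the average posterior probability of group assignment" (0.70 or higher recommended), plus closeness of theoretical and assigned proportions.

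The article expects the projected sample to yield up to 5 to 7 distinct trajectories, "providing a detailed view of the heterogeneity of longitudinal change and of factors contributing to trajectory of change". It states no person effect within groups, no one-population comparator and no comparison of slopes between groups. Mixed models appear once, as an option: "Additional multivariate approaches may be warranted, such as mixed models", for assessing the impact of key variables on longitudinal change.

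The Background shows why change matters to the investigators: they propose that "declines in cognitive ability compared to the individual’s own baseline will be the most useful trigger for intervention".

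**The concern.** The rule compares group-based models only with each other. If all members of a group share one curve and residuals are independent, the one-group model says that people do not differ even in their stable level. Any ordinary lasting spread in cognitive ability defeats that model, and the method then cuts a continuous spread into bands. The posterior-probability and proportion criteria check how cleanly people fall into bands, not whether the bands differ in change.

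At stake is the interpretation of Aim 1. If the groups are bands of level, factors associated with membership may be factors associated with level, yet the article would have them described as contributing to the trajectory of change.

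**Working it through.** **Inputs from the article**
- Size and visits: "A total of 900 participants will be comprehensively assessed and followed longitudinally at 9 month intervals over a 3 year period (four assessments"). Four visits 9 months apart span 3 × 9 = 27 months, as in the abstract ("A total of 900 participants will be characterized prospectively over a 27-month period to answer questions about the evolution of outcomes of interest"), so visits were set at 0, 9, 18 and 27 months.
- Four visits meet the article's own condition for the method: "This analysis is optimized with four or more time points".
- Scale: "Because the new measure, B-CAM, is mapped to a standard normal distribution (on a logit scale"), so a normal outcome with SD 1 was used.

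**Assumed inputs**
- GBTA without person effects within groups, and a common residual variance.
- ICC, varied from 0.2 to 0.9.
- Complete data and normal errors.

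**The article's own figure.** The number of up to 5 to 7 comes with a citation but no formula or inputs, so it cannot be reproduced.

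**Step 1. Why one group never wins.** Let everyone have the same course of change, with ICC ρ and four visits. The expected gain in twice the log-likelihood of a random-intercept model over the one-group model is about −900 × ln[(1−ρ)³(1+3ρ)]. The extra parameter costs ln 900 = 6.8 BIC points.
- ρ = 0.2: −900 × ln(0.8192) = 179.5; net 172.7
- ρ = 0.5: −900 × ln(0.3125) = 1046.8; net 1040.0
- ρ = 0.7: −900 × ln(0.0837) = 2232.5; net 2225.7

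The GBTA finally selected was on average only 24, 57 and 95 BIC points behind the random-intercept model at these ICCs (Step 2). The groups therefore recover most of the one-group model's deficit by imitating a continuous spread of levels.

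**Step 2. Number of groups with identical change for everyone.** Twenty data sets per ICC, common slope −0.1 per visit, linear group curves, 1 to 7 groups, chosen by BIC (n = 900):

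| ICC | Groups chosen (data sets) | Mean of the lowest group posterior probability | BIC, selected GBTA minus one-class random intercept (mean) | Equal-slope test rejects |
|---|---|---|---|---|
| 0.2 | 2 (15), 3 (5) | 0.79 | 24 | 1/20 |
| 0.3 | 3 (20) | 0.77 | 35 | 2/20 |
| 0.5 | 4 (16), 5 (3), 6 (1) | 0.79 | 57 | 2/20 |
| 0.6 | 4 (2), 5 (18) | 0.80 | 70 | 1/20 |
| 0.7 | 5 (1), 6 (16), 7 (3) | 0.80 | 95 | 2/20 |

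Other simulations agree.
- With no change in anyone and at most 7 groups: at ICC 0.5, 4 groups in 43 of 60 runs and 5 in 17; at 0.7, 5, 6 or 7 groups in 1, 16 and 3 of 20; at 0.8, 6 or 7 groups in 1 and 19 of 20. Every group's average posterior probability was at least 0.70 in every run.
- With up to 9 groups allowed (16 data sets per setting), 7 to 9 were chosen at ICC 0.8, and 9, the maximum tried, in nearly all fits at 0.9. Constant and quadratic curves gave similar numbers to linear ones.
- Assigned and model proportions differed by at most 0.02 on average.

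**Step 3. What the groups look like.** At ICC 0.5 to 0.7 with linear curves, group levels spanned about 2.9 to 4.2 SD. When the true change was 0, fitted 27-month changes ranged only from about −0.16 to +0.18 SD. In the Step 2 data sets BIC preferred a common slope over group-specific slopes in 20 of 20 at each ICC.

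**Step 4. With person-specific levels allowed.** A mixture with a random intercept within classes, fitted with 1 to 3 classes, selected one class in 20 of 20 data sets at each ICC in the table.

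**The case against.** A reader might infer that Aim 1 is bound to report false heterogeneity of change. The documents do not support that. The rule covers the shape of trajectories as well as their number, and Step 3 shows that null groups come out mostly near-parallel, which an analyst who looks at the fitted curves would see. The rule also lists theory first, and a simulation of the numerical criteria cannot test that part. What stands is that no comparison of slopes is stated and that the text ties the trajectories directly to heterogeneity of change.

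A second tempting reading is that the article's 5 to 7 is the number that null data produce. That match depends on an ICC of about 0.5 to 0.7, which the article does not give, and the words up to can be read as what the sample can support.

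A third is that membership predictors would mostly be predictors of level. No covariates were simulated, so this is a possibility and not a result.

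Residual structure and comparator models are details that an article may leave to a fuller plan. The longitudinal structural equation model also gives Aim 1 a second route to questions about change. Both points are fair and limit the consequence. However, the article itself states the selection rule and how its result is to be read, and the second does not follow from the numerical part of the first.

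Finally, the random-intercept comparator's success is partly built in, because the data were generated from that model. No run contained true change groups, so how often a stricter rule would miss them is unknown. This argues against making the BIC of a random-effects mixture a mandatory gate. It does not argue against reporting the comparison.

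**Conclusion.** The concern holds in a limited form. Under standard GBTA without person effects within groups, BIC, average posterior probability and agreement of proportions do not distinguish stable levels from differing change. More than one group was selected throughout ICC 0.2 to 0.9 although everyone changed identically; the count ran from 2 to at least 9 and depends on the assumed ICC. The number of groups is therefore not evidence of heterogeneous change. False heterogeneity could be reported, but need not be, because near-parallel groups are recognisable once slopes are examined. The result rests on small simulations (16 to 60 data sets per setting), complete data and normal errors. It should be corrected, and GBTA need not be abandoned.

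**What to change.** Keep GBTA and amend the Aim 1 text as follows.
- Fit a one-population linear mixed model to the same data, with a random intercept and then a random intercept plus slope. Report its BIC and slope variance beside the GBTA results.
- Compare group-specific with common slopes. Claim heterogeneity of change, or predictors of change, only if slopes differ between groups or the slope variance is supported. Otherwise describe the groups as bands of level.
- Reword the sentence expecting up to 5 to 7 trajectories, so that the number of groups is not itself read as heterogeneity of longitudinal change.
- Optionally, add a mixture with random intercepts within groups as a sensitivity analysis.

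The cost is wording and one or two extra models on data already collected, using a model class the article already mentions. The downside is that the study may report fewer distinct change groups, or none.

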#### Aim 2. To contribute evidence for the validity of a brief brain health assessment approach (B-CAM)

The strength of the relationship between the results of the reference standard cognitive assessment and the B-CAM will be tested using rank correlation and sensitivity and specificity. To formally estimate the sensitivity and specificity of B-CAM, we will use the classical method of Begg and Greens [41], which assesses diagnostic tests when there are different verification probabilities. Because the new measure, B-CAM, is mapped to a standard normal distribution (on a logit scale), it is possible to use the distribution to identify a cut-point for further testing. Validation will take place on the first 500 consecutive persons enrolled. The sample size for this estimation is based on the formula provided by Begg and Greens for sensitivity, specificity and corresponding 95 % confidence intervals (CI). Assuming that approximately 40 % of people will score in a range indicative of cognitive deficit on B-CAM, we will recruit 100 % of all those with B-CAM evidence of deficit (500 * 0.4 = 200) plus 20 % of the remainder (300 * 0.2 = 60). With this verification strategy, and under the assumptions above, the estimated sensitivity is 0.86 (95 % CI: 0.73 to 0.93). The corresponding values for specificity are 0.93 (95 % CI: 0.89 to 0.96). We will also estimate the effect of covariate status (age, co-infection with hepatitis C, history of drug use, recent immigrant, or low education) on sensitivity and specificity.

#### Aim 3: to contribute evidence for the feasibility, effectiveness potential, and acceptability of interventions holding promise for optimizing brain health

The analysis for all of the intervention trial cohorts is a mix of within- and among-cohort contrasts including contrasts with those eligible for selection, but not selected, who can serve as controls. We have designed these pilots to identify the proportion with a cognitive response rather than calculating an average response and comparing averages over time or between cohorts. This responder-status analysis provides more relevant information both at a group level and at an individual level. As the time frames for each pilot may be different, the definition of a responder can reflect these differences. For example, responder-status could be defined immediately post-intervention or at follow-up or both. With a simple responder-status analysis, it is possible to calculate the probability of achieving a certain responder proportion, which will be useful for designing future trials.

For between-group comparisons, logistic regression will be the global approach to analysis with responder-status (yes-no, defined the same way for intervention and control cohorts) as outcome. The exposure is cohort: intervention vs. control. The control group is likely much larger than the intervention cohorts, so comparing each cohort to the control is statistically reasonable. People may not complete all of a given intervention, which may affect opportunity for change; a restricted analysis will be conducted on those completing at least 60 % of the sessions, recognizing that power is reduced but the information nonetheless valuable for the design of future studies.

Generalized estimating equations (GEE) will also be applied as a secondary, more general approach that permits other time points to be modeled, and consideration of other outcomes. This accommodates either binary (responder status) or continuous (scores on cognitive tests) outcomes. This analysis uses a regression model, but clustering of outcomes within time is controlled. For binary outcomes, the effect of group (intervention or control) is expressed as an odds ratio; for continuous outcomes the parameter is an effect size equivalent to an adjusted paired-*t*-test. An interaction term tests whether the effect differed by group (i.e. was larger in the intervention group, as hypothesized).

Additional analyses will be used to explain changes in cognitive status as a function of changes expected from the intervention. As the intervention cohorts are small, we will use concordance parameters, rather than a regression model, to quantify the degree to which changes in hypothesized mechanisms by which the interventions operate (improving exercise capacity, physical activity, healthy living) are concordant (at the individual level) with changes in the outcomes (cognitive ability or self-efficacy for self-management).

There were two considerations in estimating sample size. First, for the GEE analysis, a minimum sample size of 30 has been suggested [42, 43]. Second, the probability of achieving a specific response proportion can be estimated using the normal approximation to the binomial distribution when response proportions are not extreme (http://stattrek.com/online-calculator/binomial.aspx). Assuming that, in the absence of intervention, there is only a small probability of making a positive cognitive response, say 10 % (*p* = 0.10), then with 30 subjects, the probability of observing seven or more responders is unlikely, *p* < 0.03. For other outcomes (depression and anxiety) which may have a higher probability of positive response in the absence of intervention, say 20 %, then 11 or more responders out of 30 would need to be observed to be less likely than 0.05 to have occurred by chance.

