### Multiple randomized controlled trials design

All participants are provided with an information package on strategies known to have a positive effect on brain health. Our Brain Health Now Tips cover recommendations for stopping smoking, challenging the mind, limiting alcohol and street drugs, increasing physical activity, sleeping well, managing stress and negative moods, healthy eating, and the importance of telling the medical team about all current medications. In addition to this, a series of pilot interventions targeting one or more aspects of brain health are included in this study (Table 3). Each trial has its own protocol, submitted for separate ethical review. People who meet eligibility criteria are identified from the database and those from the site where the study is conducted will be offered the intervention; eligible participants from the other sites serve as controls. Two of the trials, cognitive training and the insomnia intervention, have started recruitment. For all but two of the trials, cognitive ability is the primary outcome. The trials are designed to have a common outcome definition (responder status), analysis and sample size.

**Table 3 Tab3:** Planned pilot trials for the brain health now study

Intervention	Site	Selection criteria [outcome measure]	
		B-CAM level^a^ including a self-report cognitive concern [B-CAM primary/secondary]	Other criterion
Cognitive training	Montreal	^a^[Primary]	
Insomnia intervention	All	^a^[Secondary]	Sleep dissatisfaction
Exercise	Montreal	[Primary]	Sedentary; physical function limitations
Sleep apnea intervention	Selected	[Primary]	Sleep dissatisfaction / sleep apnea screen
Goal management training	Selected	^a^[Primary]	
Cognitive behavioural therapy	Montreal	[Secondary]	Depressive symptoms
Relaxation	Montreal	[Secondary]	Anxiety

^a^indicates that selection criteria include a score lower than the mean on the B-CAM

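### The 7-of-30 and 11-of-30 planning counts are right for a one-sample binomial test but do not describe the planned intervention-versus-control logistic regression

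*Protocol article*

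**What the plan says.** The Aim 3 text gives two reasons for the pilot size. The first is a rule of thumb: "for the GEE analysis, a minimum sample size of 30 has been suggested". The second is a probability calculation, which the article says "can be estimated using the normal approximation to the binomial distribution when response proportions are not extreme". For cognition it assumes that without intervention "there is only a small probability of making a positive cognitive response, say 10"%, and concludes that "then with 30 subjects, the probability of observing seven or more responders is unlikely", with p < 0.03. For depression and anxiety, "which may have a higher probability of positive response in the absence of intervention, say 20"%, it says "then 11 or more responders out of 30 would need to be observed to be less likely than 0.05 to have occurred by chance". No source is given for either rate.

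Earlier in the same section the analysis is described differently: "For between-group comparisons, logistic regression will be the global approach to analysis with responder-status" as the outcome and intervention versus control cohort as the exposure. The control cohort is expected to be much larger than the intervention cohort, but no number is given. Within-cohort contrasts are planned as well. The section on the multiple randomized controlled trials design says the pilots share one outcome definition, analysis and sample size. The footnote to Table 3 there marks the trials whose "selection criteria include a score lower than the mean on the B-CAM": cognitive training, insomnia and goal management training. B-CAM is the primary outcome in the first and third of these.

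**The concern.** The calculation offered for 30 per pilot answers this question: if the untreated rate is known to be exactly 10% (or 20%), how surprising are 7 (or 11) responders? The planned between-group analysis asks another: do responders occur more often than in a control group whose rate is itself estimated? The second question carries more uncertainty, so the same count is weaker evidence.

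The one-sample calculation also leans entirely on the assumed rate. Where people enter because of a low score on the measure that later defines response, some will improve through regression to the mean alone. A fixed benchmark cannot absorb that, whereas controls selected in the same way can.

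At stake is how pilot results are read. The article says responder proportions will inform the design of future trials. A reader who takes seven responders as an event with under 3% probability by chance may carry forward more confidence than the planned comparison would give. Because the sample size is common to all pilots, the same reasoning carries across the programme.

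**Working it through.** **Inputs.** From the article: 30 per pilot, null rates 0.10 and 0.20, counts 7 and 11. Assumed here because the article gives no figure: 30 to 300 controls, an observed control rate equal to the null rate, two-sided 0.05, and test-retest correlation r from 0.6 to 0.9.

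**1. The article's own figures.** With X binomial(30, p):
- p = 0.10: P(X ≥ 7) = 0.0258 and P(X ≥ 6) = 0.0732.
- p = 0.20: P(X ≥ 11) = 0.0256 and P(X ≥ 10) = 0.0611.

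Both statements reproduce, and 7 and 11 are the smallest counts with a one-sided tail below 0.05. The normal approximation with continuity correction gives 0.0166 and 0.0200, also within the stated limits.

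**2. Sensitivity to the assumed rate.** P(X ≥ 7) is 0.061 at 12% and 0.153 at 15%. P(X ≥ 11) is 0.106 at 25% and 0.270 at 30%.

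**3. The two-group test.** In an unadjusted logistic model with a responders of 30 and c responders of n controls, log OR = ln[a(n − c) / ((30 − a)c)] and SE = √[1/a + 1/(30 − a) + 1/c + 1/(n − c)].

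Example with n = 100:
- 7/30 against 10/100: log OR = ln(7 × 90 / (23 × 10)) = 1.008; SE = √(1/7 + 1/23 + 1/10 + 1/90) = 0.545; z = 1.85; two-sided p = 0.065.
- 11/30 against 20/100: log OR = ln(11 × 80 / (19 × 20)) = 0.840; SE = √(1/11 + 1/19 + 1/20 + 1/80) = 0.454; z = 1.85; p = 0.064.

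| Controls (assumed) | p, 7/30 vs 10% | p, 11/30 vs 20% | Smallest counts with p < 0.05 |
|---|---|---|---|
| 60 | 0.098 | 0.092 | 8 and 12 |
| 100 | 0.065 | 0.064 | 8 and 12 |
| 150 | 0.048 | 0.051 | 7 and 12 |
| 200 | 0.041 | 0.045 | 7 and 11 |
| 300 | 0.033 | 0.038 | 7 and 11 |

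With only 30 controls the two p-values would be 0.18 and 0.16.

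**4. Power of that comparison.** Power = Φ[(Δ − 1.96·se₀)/se₁], with se₀ pooled and se₁ unpooled. For a true 23.3% (7/30) against 10% and 100 controls: Δ = 0.133, se₀ = 0.0702, se₁ = 0.0828, so power = Φ(−0.05) = 0.48. With 30 controls it is 0.28 and with 300 it is 0.58. For a true 30% against 10% it is 0.49, 0.735 and 0.82 with 30, 100 and 300 controls.

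**5. Regression to the mean.** Let baseline x and follow-up y be standard bivariate normal with correlation r, and let response be d = y − x ≥ k. Set k = 1.2816 × √[2(1 − r)], so that 10% of unselected people respond. Among those with x below the mean, the untreated rate is 2·P(d ≥ k, x < 0).

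| r (assumed) | Untreated rate | P(7 or more of 30) |
|---|---|---|
| 0.9 | 13.1% | 0.09 |
| 0.8 | 14.4% | 0.13 |
| 0.7 | 15.3% | 0.17 |
| 0.6 | 16.1% | 0.20 |

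**The case against.** A reader might infer that the stated p < 0.03 is wrong. It is not: the sentence is conditional on a 10% rate, and the exact tail is 0.0258.

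A reader might also take 7/30 and 11/30 as success rules. The article presents them only as a consideration in choosing the sample size, and nowhere declares a pilot positive on that count.

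It can fairly be said that much of the remedy is already planned. Controls are eligible people who were not offered the intervention, response is defined the same way in both cohorts, and logistic regression is the main between-group method. Controls meeting the same B-CAM criterion should show much the same regression to the mean, so that mechanism is not an argument against the between-group comparison. This stands, and it confines the problem to the planning figures and to any within-cohort reading.

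The choice of test also matters. Fisher's exact test gives p of 0.060 to 0.069 for 7/30 against 10% with 100 to 300 controls, but Fisher is not the stated analysis. Under the logistic Wald test the article's 7 and 11 hold with 200 to 300 controls. Sidedness matters too. The binomial tails are one-sided; halving the Wald values for 7/30 gives 0.049, 0.032, 0.024 and 0.017 with 60, 100, 150 and 300 controls. So part of the gap comes from moving to a two-sided test. With 60 or 100 controls the figure still exceeds 0.0258.

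Finally, the 10% may already be meant for the selected group, and the responder definition is left to each pilot. Nothing in the article settles either point, so the regression-to-the-mean figures are conditional. A reader might extend them to every pilot. Table 3 does not support that: exercise and sleep apnea carry no below-mean B-CAM criterion, and in the insomnia trial B-CAM is secondary. Selection on depressive symptoms or anxiety raises a similar question, but the article already uses a higher rate there and no figure is calculated here.

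**Conclusion.** The concern holds as a mismatch between the planning calculation and the analysis, not as an arithmetical error. The one-sample figures are correct at exactly 10% and 20%, but they do not give the strength of evidence or the power of the planned two-group comparison. At two-sided 0.05 with an unadjusted Wald test, 7/30 against 10% falls short with 60 or 100 controls and passes narrowly at 150. The count of 11/30 against 20% falls short up to 150 and passes at 200. If the true responder rate equals the planning count (23.3% against 10%), power stays below 0.6 even with 300 controls.

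The fixed 10% is least secure in cognitive training and goal management training. There the chance of seven or more untreated responders would be about 0.09 to 0.20, provided that 10% describes unselected people, response is change from the selection score, and r lies between 0.9 and 0.6. Control numbers, sidedness and r are assumptions of this check. For small pilots aimed at feasibility and effectiveness potential the consequence is moderate, but the sentence invites a firmer reading than the planned analysis supports.

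**What to change.** 1. Do not use the fixed 10% and 20% rates as evidence of effect within a cohort. Make the already planned comparison with controls meeting the same eligibility rule the basis for judging response.
2. Add the baseline score (B-CAM, or the relevant symptom scale) as a covariate in the logistic model.
3. Restate the planning sentence for that comparison, with the expected control number, the test and its sidedness. Under an unadjusted logistic Wald test at two-sided 0.05, and control response of 10% and 20%, the counts needed of 30 are 8 and 12 with 60 to 100 controls, 7 and 12 with 150, and 7 and 11 with 200 to 300. If another test is chosen, recompute the counts for it.
4. Give a source for the 10% and 20%, or label them as assumptions and say whether they refer to the selected group.

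The cost is wording and one covariate that is already collected. The stated counts become slightly less favourable when the control group is modest, and the baseline-adjusted result may differ somewhat from the unadjusted counts.
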